##### Disclosure of harm or potential harm

Participants may also disclose experiences of ongoing violent practices, whether as the recipient or the perpetrator of harm toward themselves, their child(ren) and/or partner that may require intervention. This study recognises that researchers have a responsibility towards safeguarding children and other individuals who may be at risk of experiencing abuse or neglect, or any other forms of severe harm. The following protocol is proposed to mitigate any actual or potential harm to children or adults that might occur during the study.

If it is disclosed that the participant (who will be aged 18 or older) has recently experienced inter-personal violence (physical, sexual, or emotional) or is at risk of experiencing inter-personal violence, and he or she would like a direct referral to a health, welfare or other services, the data collector or relevant member of the research team will abide by the following:If information in face-to-face data collection is disclosed that suggests that any member of the household is at risk of significant harm, the researcher will discuss concerns with the respondent at the end of the interview. In the self-administered outcome assessments, the referral process will be triggered based on participant survey responses that indicate potential harmful experiences and/or support needs, including experiences of violence, mental health issues, substance abuse, neglect, and food insecurity. In such cases, the participant will be contacted via phone call by a member of the research team.If the individual at risk is the participant, a member of the research team will inform the respondent that he/she may choose to self-refer (by contacting a service provider on the list of services given to the participant, or another provider of his/her own choosing) or request a direct referral to health, welfare or other services.If the participant requests a direct referral, the member of the research team will complete an adult referral form together with the participant.If the participant is in immediate danger, or his or her own emotional state is such that it places their own or a third party’s life at risk, the member of the research team will urgently share the information with the appropriate service provider (e.g. police, ambulatory service, nearest hospital).If the case does not appear to be acute, the research team member will agree upon a timeframe with the participant when the information will be shared with the appropriate service provider.If the individual at risk of harm is a child, the researcher will discuss with the parent/caregiver the options for referral to child welfare, health organisations, and other services.If the harm towards the child is considered significant, the research member will inform local child protection services immediately and the participant will be automatically excluded from the study. If authorities do not respond immediately, the researchers will follow up until assistance arrives.The research team member responsible for the referral will work with the in-country project coordinator to monitor whether the service provider has indeed responded to the request for support. Weekly supervision meetings with all field personnel will allow discussion of issues that arise concerning harm to research subjects and children.If we determine that respondents or their families have experienced significant harm as a result of participation in the study (i.e., severe abuse, suicidality, intimate partner violence, or other potential psychological or physical injuries), further research activities will be suspended until the issue has been adequately addressed and the study has been adapted accordingly.

##### Mitigating potential harm from intervention

We have also considered the potential risk of harm from participating in the intervention, and will be monitoring this throughout the project [79]. Participation in the parenting programme may potentially cause psychological harm for caregivers, particularly when they confront difficult experiences from their own childhood or deal with intimate partner violence at home. However, past research on parenting interventions, including numerous randomised trials conducted in LMICs [11], have consistently shown no evidence of harm and abundant evidence of benefits for both parents and children, as well as high levels of parent satisfaction. To ensure a comprehensive understanding of the potential outcomes of the parenting programme, this study will explicitly examine both the benefits and risks of the intervention. Our statistical analysis plan includes two-tailed tests to assess the differences between groups and examine potential positive and negative effects of the intervention. We will also use qualitative analysis to explore the experiences and perspectives of participants regarding the intervention and its effects.

We anticipate no direct harm as a result of withdrawing from the intervention, as participation in the programme is completely voluntary, with no direct penalties for non-participation. Furthermore, other studies, including evaluations in other low-resource settings [11], have shown no evidence of harm resulting from the termination of parenting interventions. In the unlikely event of significant harm being observed in any of the intervention conditions, we will suspend the implementation of the programme until the harm has been adequately addressed, and the programme has been modified accordingly.

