##### Parental depression (moderator)

Three items from the Centre for Epidemiologic Studies Depression Scale (CES-D 10) [69] will be used to assess caregiver depression. The items ask caregivers to respond how they have felt in the previous week (3 items, e.g., “felt that everything you did was an effort”). Caregivers respond on a frequency scale ranging from 0 to 7 days. Items are summed with higher scores indicating greater parental depression.

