##### Parenting stress (moderator)

One item adapted from the Parenting Stress Scale [70] will be used to assess caregiver stress. The item asks, “how many times in the past month did caring for your children make you feel very stressed” The items will be rated on a frequency scale of 0 to 8 or more times.

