##### Objective 4: To conduct exploratory analyses of the potential impact of components and combination of component levels on caregiver behavioural outcomes (e.g., child maltreatment, positive parenting, parental communication about sexual abuse prevention)

Engagement is a precursor to behaviour change. We will therefore investigate whether experimental components designed to enhance engagement also impact caregiver behavioural outcomes at post-intervention. Using the same generalised linear mixed effects models outlined above, we will examine the main and interaction effects of intervention components on the core ParentApp targets: reducing child maltreatment, improving positive parenting and supervision, and increasing parental communication about sexual abuse prevention. Covariates will additionally include baseline assessments of each outcome. We may also conduct exploratory mediation analyses to generate learning around which engagement variables mediate programme impacts.

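### The protocol names psychological harm to caregivers and promises two-tailed tests of risk, but plans no comparison of caregiver distress between component levels

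*Protocol article*

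**What the plan says.** The section on mitigating potential harm from the intervention names a specific harm: "Participation in the parenting programme may potentially cause psychological harm for caregivers, particularly when they confront difficult experiences from their own childhood". It adds living with intimate partner violence as a second trigger. It then commits that "this study will explicitly examine both the benefits and risks of the intervention", with two-tailed tests of group differences as the quantitative means and qualitative analysis beside them.

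The measures section gives each scale a role in its heading. Child maltreatment, positive parenting and communication about sexual risk are each headed as exploratory outcome and moderator. The two distress measures are headed as moderator only. For depression, "Three items from the Centre for Epidemiologic Studies Depression Scale (CES-D 10) [69] will be used to assess caregiver depression". For stress, "One item adapted from the Parenting Stress Scale [70] will be used to assess caregiver stress".

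Under Objective 4, "we will examine the main and interaction effects of intervention components on the core ParentApp targets: reducing child maltreatment, improving positive parenting and supervision", followed by communication about sexual abuse prevention. Objective 5 brings in stress and depression as baseline severity, to test whether they modify component effects.

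On individual safety, the disclosure section says: "In the self-administered outcome assessments, the referral process will be triggered based on participant survey responses". Mental health issues are among the listed triggers.

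**The concern.** A two-tailed test examines a harm only if it is run on a variable that reflects that harm. The article makes the promise, names the harm and describes four questionnaire items close to it, then assigns those items a role in which no effect on them is estimated. Followed as written, the two-tailed tests run on engagement and on parenting behaviour, and none runs on caregiver distress.

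The selection of the final package under Objective 8 makes this matter. A component level passes through main effects on engagement, then cost-effectiveness, then acceptability and feasibility. Suppose one level, such as moderated group discussion or open access to all modules, left caregivers more distressed than the alternative. The quantitative results would not show it. The harm section also provides for suspending the programme if significant harm is observed in any condition, yet the article names no by-condition measure of the harm it singles out, and no external data monitoring committee is planned.

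**Working it through.** The plan states no figure on this point, so the first check sets the sections side by side.

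| Measure | Role in its heading | Outcome in Objective 4 | Use in Objective 5 |
|---|---|---|---|
| Child maltreatment (4 items) | exploratory outcome, moderator | yes | baseline moderator |
| Positive parenting and supervision (5 items) | exploratory outcome, moderator | yes | baseline moderator |
| Sexual-risk communication (3 items) | exploratory outcome, moderator | yes | possible moderator, by its heading |
| Parental depression (3 items) | moderator | no | baseline moderator |
| Parenting stress (1 item) | moderator | no | baseline moderator |

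The primary and secondary engagement outcomes add nothing on distress: they are launches, workshops or modules completed or started, home practice, time on the app and ParentPoints. Neither distress measure therefore has an outcome analysis, while all three parenting domains do.

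The second check asks how precise the missing comparison would be.

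Inputs from the article: 16 clusters of about 40 caregivers (16 × 40 = 640); three two-level components, so 8 clusters per level; two-sided alpha 0.05. The 80% power is the target used in the article's own power section.

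Assumptions, since the article gives none of these: ICC 0.01 to 0.05; correlation 0.5 between baseline and endline scores; endline respondents per cluster m = 40, 20 or 10. The lowest value is 25% of 40. It echoes the South African self-guided pilot, where as few as 25% were still engaging after the first session.

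Standard error of a component contrast, in SD units:

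SE = √( (4/16) × [ICC + (1 − ICC)(1 − 0.5²)/m] )

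Residual degrees of freedom: 16 clusters − 4 fixed parameters (intercept and three components) = 12. The multiplier for 80% power is t(0.975; 12) + t(0.80; 12) = 2.179 + 0.873 = 3.05.

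| m | ICC | Bracketed term | SE | Detectable difference (SD) |
|---|---|---|---|---|
| 40 | 0.01 | 0.01 + 0.99 × 0.75/40 = 0.0286 | 0.0845 | 0.26 |
| 40 | 0.05 | 0.05 + 0.95 × 0.75/40 = 0.0678 | 0.130 | 0.40 |
| 20 | 0.01 | 0.01 + 0.99 × 0.75/20 = 0.0471 | 0.109 | 0.33 |
| 20 | 0.05 | 0.05 + 0.95 × 0.75/20 = 0.0856 | 0.146 | 0.45 |
| 10 | 0.01 | 0.01 + 0.99 × 0.75/10 = 0.0843 | 0.145 | 0.44 |
| 10 | 0.05 | 0.05 + 0.95 × 0.75/10 = 0.121 | 0.174 | 0.53 |

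A version without baseline adjustment, (2.179 + 0.873) × √(2 × [1 + 39 × ICC]/320), gives 0.28 to 0.41 SD at full retention. The correlation assumption therefore matters little there.

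**The case against.** The strongest reply is that the plan does look for this harm. Survey responses on mental health trigger a phone call and possible referral, weekly supervision meetings discuss harm, the coordinating team monitors safety, significant harm leads to suspension, qualitative work covers the effects of the intervention, and responses to emotional check-ins may be described. All of that stands. A reader might infer that the harm would never be estimated or reported, and the documents do not support that. A reader might also infer that a component level could be chosen on engagement alone. That too is unsupported, because Objective 8 adds cost-effectiveness and acceptability steps. None of these routes, however, is described as giving a difference between component levels, which is what the promise of two-tailed tests implies.

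Second, the two-tailed promise is not empty: child maltreatment is an outcome, and a two-sided test could show it worsening. This is right, but it concerns a different harm.

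Third, the statistical analysis plan is not shown, and Objective 4 introduces its outcomes with an e.g. in its title. The omission of detail would indeed be no finding. Here, however, the article itself assigns the roles, in contrasting headings, and the Objective 4 text then lists its targets without qualification. An analysis plan that follows it inherits the gap.

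Fourth, the fix has limits. All eight conditions use the app, so no contrast isolates harm from the programme. The four items do not ask about childhood experiences or partner violence. Endline questions sit in the last workshop or module, so caregivers who stopped because of distress are likely to be missing. Table 2 is not shown, so it is unverified whether these items are asked at endline at all. These points stand and limit what the added analysis can claim.

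**Conclusion.** The point holds in a bounded form. The article promises a quantitative look at risk and names psychological harm to caregivers, but gives its two distress measures only a baseline moderator role and lists no distress outcome. The sections need reconciling. The finding concerns exploratory and safety reporting and changes no primary inference.

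The added comparison would be useful but not decisive. At full retention it could detect about 0.26 to 0.40 SD between levels of a component, and at 10 respondents per cluster about 0.44 to 0.53 SD, under assumed ICCs of 0.01 to 0.05 and a baseline correlation of 0.5. A null result at the lower retention would offer little reassurance. A reader might take a component contrast on depression or stress as a test of whether the programme harms caregivers. The design cannot support that, for want of an app-free condition.

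**What to change.** 1. Relabel parental depression and parenting stress as exploratory (safety) outcome, moderator.
2. Add both to the Objective 4 outcomes, using the planned mixed model with the baseline value as covariate, and report the three component contrasts with 95% confidence intervals.
3. Tabulate by condition how many caregivers worsen from baseline and how many have no endline value.
4. State beside these results that they describe differences between component levels among endline responders, not harm from the programme, and that precision is limited.

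The cost is a few lines of plan wording, two more exploratory models and one table. If Table 2 shows the items at baseline only, four short items must also be added to the endline form. If that is not feasible, the alternative is to narrow the promise in the harm section so that it names only the qualitative, referral and monitoring routes for caregiver distress.

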##### Self-Referral

In addition to our referral procedure described above, the app includes local self-referral and emergency contacts which are affordable and remote-friendly. This information will include services for family and child support, substance use, gender-based violence and rape, child abuse and protection, physical, mental, and contact details for available helplines. These resources were identified by the research team following a thorough mapping of online and affordable support systems in Tanzania.

### Dissemination plans

Findings will be shared with policy makers, government stakeholders, community-based organisations, and community members. Results will also be published in open-access peer-reviewed journals and presented at conferences. Authorship of publications from this study will follow the guidelines recommended by the International Committee of Medical Journal Editors. All components of this research, including the research protocol, study assessments, anonymised datasets, and statistical code will be made available on the Open Science Framework.

In addition to academic dissemination and policy engagement, community dissemination and participant feedback will be prioritised. Brief reports in lay language summarising the study findings will be created, focusing on the findings relevant to NGOs and government working with caregivers and adolescents. These reports will be presented to local community groups, NGOs, and health services. Researchers will also report back verbally to participants, encouraging their thoughts and feedback on emerging findings. For example, the later stages of the qualitative research will ask participants to respond to some of the quantitative findings, which will serve as a form of feedback. No identifiable details will be given in any dissemination or feedback.

## Discussion

This trial is the first of its kind to optimise engagement strategies for a digital parenting intervention in a LMIC. It involves a pragmatic cluster randomised factorial experiment and an innovative mixed-methods analytic approach to inform the selection of the most effective, cost-effective and feasible engagement package for ParentApp, implemented among vulnerable caregivers of adolescents in Tanzania. By examining the role of human support, app design, and a digital literacy training in reducing barriers to programme participation, this study promises to provide key insights into engagement and effectiveness whilst tailoring to vulnerable population needs, delivery challenges, and best-practises for scale-up. Furthermore, findings may also identify potential moderators that could provide understanding about effective engagement strategies for different subpopulations such as fathers. Thus, this novel trial has the potential to inform pragmatic implementation strategies for digital interventions, specifically as they relate to engaging and retaining vulnerable families in digital public health prevention services in LMICs.

## Protocol amendments

The current protocol version is 1.0 (24/10/2022). Any significant subsequent protocol modifications will be submitted to the study investigators and the Institutional Review Boards for approval.

## Data Availability

ParentApp for Teens is freely available and open source online. Anonymised datasets will be made available via an open-access repository such as the Open Science Framework (https://osf.io/).

## Abbreviations

VAC: Violence against children
LMICs: Low- and middle-income countries
NGO: Non-governmental organisation
MOST: Multiphase optimisation strategy
RCT: Randomised controlled trial
PLH: Parenting for Lifelong Health
NIMR: National Institute for Medical Research in Tanzania
ICS: Investing in Children and Strengthening their Societies
FGDs: Focus group discussions
IDEMS International: Innovations in Development, Education, and the Mathematical Sciences
INNODEMS Kenya: Innovations in Development, Education, and the Mathematical Sciences
IRR: Incidence rate ratio
OR: Odds ratio
TSC: Trial Steering Committee
